### Follow-up

Treatment outcomes will be estimated at baseline (week 0) and after intervention for 2 days (T1), 4 weeks (T2), 12 weeks (T3) and 24 weeks (T4). We will call each participant to keep in contact and remind them of the next interview to avoid being lost to follow-up.

### Intervention

After baseline estimations (days 1–2), patients will receive active or sham-iTBS for 10 consecutive days (days 3–12).

### iTBS + PT group (study group)

During each treatment, the patient will receive 3 min and 20 s of iTBS stimulation, twice daily, and PT once a day (Fig. 2).

**Fig. 2 Fig2:**
[figure not shown]
The iTBS + PT group

ITBS (Magstim Rapid^2^, Whitland, UK) will use standard, internationally approved parameters: 80% resting movement threshold (RMT) stimulation intensity; triplet 50 Hz bursts, repeated at 5 Hz for 2 s on and 8 s off, 10 times; 600 pulses per session; for a total duration of 3 min 20 s.

For the RMT measurement, the centre of the figure-of-eight coil is aimed at the base of the scalp of the cerebral cortex movement area, the patient is told to completely relax, and the transcranial magnetic stimulation output intensity is gradually adjusted. Ten consecutive single stimulations can induce five movement evoked potentials with an amplitude greater than 50 V minimum stimulation intensity; or 10 stimulations, at least five times, will cause the minimum intensity of the left thumb muscle contraction [40]. The frameless stereo optical tracking and navigation system is used for positioning. We will conduct dynamic real-time monitoring throughout the treatment process to ensure the accuracy of the target. To obtain stimulation target M1, all participants will undergo MRI brain scans prior to the study: the target is a spherical image centred on the centre point of the M1 surface in a standard brain template based on T1-weighted anatomical magnetic resonance structural images. The target of M1 is transformed into an image of the brain structure of each individual, which is then introduced into a frameless neuronavigation system (Brainsight, Brainbox Ltd, Cardiff, UK).

The coil remains horizontal and tangential to the skull, pointing forward, with its centre point overlapping the target of M1 [41, 42]. Initial treatment consists of twice-daily sessions (on week days; i.e., five sessions a week).

PT is performed in the hospital, consisting of four types of treatments of 30 min each day for 10 days, 6 days of PT consist of session 1, session 2 and session 3 at weekdays; the other 4 days of PT consist of session 4 at weekends. The first treatment is one-on-one physical therapist treatment. It includes cardiovascular warm-up activities, active and passive movements to improve the range of motion of joints, stretching of the abdominal muscles, strengthening of the paraspinal muscles, changes in posture, and movements of balance and posture control. The second session will use a Biofeedback Balance Instrument to improve balance, 30 min a day. Balance training has been successfully used to improve balance in neuropathic patients [43-46], which initiates stabilising responses to postural perturbations and is likely to improve trunk control [47]. It is certainly related to balance and equilibrium and is appropriate to challenge the sensorimotor integration mechanisms [48].

The third session will use a variety of special equipment to improve gait and balance: a stable treadmill with biofeedback (multiple instruction persistence designed according to the principle of virtual reality); walking and gait training under the interference of virtual multiple obstacles and exogenous signals (C-mill); and a treadmill enhancement (treadmill training with auditory cues and feedback). The maximum treadmill speed is 3.5 km/h; patients train on a treadmill for no more than 30 min a day. The fourth session will use gymnastics designed by the physiotherapists [name] specifically for patients with Parkinson's disease. This gymnastics can improve the patient’s balance, gait and mobility**.**

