### Sham-iTBS + PT group (control group)

During each treatment, the patient performs approximately 3 min and 20 s of sham-iTBS, twice daily, and PT once a day (Fig. 3). On sham stimulation, an eight-word false stimulation coil that can simulate sound and touch, such as Air film, which does not induce any significant physiological transcranial effect on the brain, will be used. The sham parameters will be set to 80% RMT, 50 Hz, 3 intra pulses, 5 Hz and 200 stimulus clusters [49]_._ Treatment will be twice daily. The PT training method and duration are as for the study group.

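### The active stimulation session does not multiply out (10 cycles give 300 pulses in 100 s, not 600 in 3 min 20 s), and weekday-only sessions contradict 10 consecutive treatment days

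*Protocol article*

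**What the plan says.** All references are to the protocol article.

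**The session.** The stimulation paragraph of the iTBS + PT group section (after the Fig. 2 caption) gives 50 Hz triplets at 5 bursts per second, "2 s on and 8 s off, 10 times; 600 pulses per session; for a total duration of 3 min 20 s", all in one sentence. The opening line of that section also gives 3 min 20 s, twice daily. The Sham-iTBS + PT group section gives about the same duration, three pulses per cluster, and "5 Hz and 200 stimulus clusters".

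**The calendar.** The Intervention section says that "patients will receive active or sham-iTBS for 10 consecutive days", and identifies these as days 3–12. The Abstract gives twice-daily stimulation for 10 days. The stimulation paragraph instead says: "Initial treatment consists of twice-daily sessions (on week days; i.e., five sessions a week". The physiotherapy description that follows assigns 6 of its 10 days to weekdays and says "the other 4 days of PT consist of session 4 at weekends".

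**The concern.** Both conflicts lie in the operative definition of the experimental treatment. An operator who programs the stimulator by number of cycles and one who programs it by number of pulses would deliver sessions that differ by a factor of two. A site that follows the weekday sentence and one that follows the Intervention section would treat on different days and could deliver different numbers of sessions.

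The protocol itself treats total dose as relevant: its Discussion cites a meta-analysis in which more courses and higher pulse totals went with better motor outcomes. If the delivered course varies between patients, or cannot be stated, a positive or null result is harder to interpret and to reproduce. Under Trial status the first patient was enrolled on April 14, 2022, so patients may already have been treated under the present wording.

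**Working it through.** **1. Pulses and duration of one active session**

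Inputs from the stimulation paragraph: 3 pulses per burst, 5 bursts per second, 2 s on, 8 s off, 10 cycles. Stated totals: 600 pulses and 3 min 20 s = 200 s.

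- Pulses per train: 3 × 5 × 2 = 30.
- Length of one cycle: 2 + 8 = 10 s.
- Ten cycles: 10 × 30 = 300 pulses and 10 × 10 = 100 s. The stated totals are not reproduced; both come out at half.
- Cycles needed for the stated totals: 600 / 30 = 20 and 200 / 10 = 20. The two stated totals agree with each other.

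Other readings:

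- Dropping the last off-period gives 100 − 8 = 92 s for 10 cycles and 200 − 8 = 192 s for 20. This does not close the gap.
- Keeping 10 cycles and both totals would need 600 / 10 = 60 pulses per train (not 30) and 200 / 10 = 20 s per cycle (not 10). Both contradict the stated parameters.
- Reading the 10 as bursts per train (5 × 2 = 10) gives 600 / (3 × 10) = 20 trains and 20 × 10 = 200 s, so everything agrees. But in "2 s on and 8 s off, 10 times" the count follows the on/off pattern and reads as a number of cycles.

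Sham: 200 clusters × 3 pulses = 600 pulses. If the sham uses the same on/off pattern, which its section does not state, that is 200 / 10 = 20 cycles and 200 s, matching its stated duration.

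**2. Treatment days**

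For each start day, the weekdays and weekend days in a run of 10 consecutive days are counted. Weekday-only sessions are weekdays × 2.

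| First stimulation day | Weekdays | Weekend days | Weekday-only sessions | Pulses at 600 | Pulses at 300 |
|---|---|---|---|---|---|
| Mon, Tue, Wed | 8 | 2 | 16 | 9,600 | 4,800 |
| Thu, Sun | 7 | 3 | 14 | 8,400 | 4,200 |
| Fri, Sat | 6 | 4 | 12 | 7,200 | 3,600 |

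All 10 consecutive days: 10 × 2 = 20 sessions, which is 12,000 pulses at 600 or 6,000 at 300.

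- No start day gives a run without weekend days, so the weekday restriction and days 3–12 cannot both hold.
- The physiotherapy split of 6 weekdays and 4 weekend days fits 10 consecutive days with a Friday or Saturday start. On that calendar, weekday-only stimulation would leave 4 of the 10 physiotherapy days without stimulation, although the group description pairs twice-daily stimulation with daily physiotherapy.
- Ten weekday treatment days would keep 20 sessions but take 12 calendar days from a Monday start, or 14 from a Tuesday to Friday start. Counting from day 3, treatment would end on day 14 or 16, not day 12.
- Twice daily on five weekdays is 2 × 5 = 10 sessions a week, not five, unless sessions there means days.

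**The case against.** The best defence is that both problems are slips in a single paragraph. The 600 pulses, the 3 min 20 s (stated twice for the active arm) and the sham setting all agree, and only the cycle count stands apart. The 10 consecutive days are supported by a physiotherapy calendar that includes weekends, and only the weekday sentence stands apart. This is fair as to where the errors probably lie. It does not remove them: the paragraph is the one that sets the stimulation parameters, and agreement among the other figures does not establish what was programmed or delivered. Calling the treatment initial does not help either, because no later stimulation phase is described.

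A reader might draw three stronger conclusions that the documents do not support:

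- **Active sessions visibly shorter than sham sessions, which would threaten blinding.** The stated durations are the same in both arms. A 100 s active session appears only if the cycle count is allowed to override two explicit statements of duration.
- **A four-fold spread in total dose, 3,000 to 12,000 pulses.** The low end is 10 sessions × 300 pulses. It needs one session a day, whereas twice daily is stated throughout, including in the weekday sentence itself.
- **A per-protocol set that cannot be defined.** The Dropping criteria cover patients who do not finish training. The Statistical analysis section makes intention-to-treat primary and per-protocol secondary and conditional. Detailed adherence rules commonly sit in the full protocol or SAP, which are not shown.

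The physiotherapy split is likewise not a contradiction in itself, since a Friday or Saturday start satisfies it.

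**Conclusion.** The point holds as two internal contradictions in the definition of the active treatment. First, the stated cycle count gives exactly half of the stated pulses and duration. Second, weekday-only sessions cannot be reconciled with stimulation on each of days 3–12, and they do not fit a treatment calendar that includes weekend days.

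At 600 pulses per session, the calendar conflict leaves the course at 12,000 pulses or at 7,200 to 9,600, that is 20% to 40% fewer (9,600 / 12,000 = 0.80; 7,200 / 12,000 = 0.60). This assumes twice-daily sessions and, for the lower range, that no sessions are moved beyond day 12. The literal cycle count would halve every total.

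What is affected is the definition, delivery and reporting of the treatment. The primary intention-to-treat comparison and the calculation of 21 patients per group do not use these figures. The arithmetic shows which figures agree with one another; it does not show which dose or schedule is right.

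**What to change.** The sponsor should reconcile the Abstract, the Intervention section and both group descriptions, so that they give:

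- one set of cycles, pulses and duration that multiply out;
- one statement of treatment days and total sessions, consistent with the day numbering and the physiotherapy calendar, and clear on whether a session is a single stimulation or a treatment day;
- the same session timing and calendar for both arms.

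The sponsor should also check from treatment records what has been delivered since recruitment began in April 2022, and report delivered sessions and pulses by arm with the results. No dose or schedule is proposed here.

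The cost is a text correction, which the Data monitoring section requires the ethics committee to approve if it amends the protocol, and a review of existing records. The sample size and the primary analysis do not change.

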### Sham-iTBS + PT group (control group)

During each treatment, the patient performs approximately 3 min and 20 s of sham-iTBS, twice daily, and PT once a day (Fig. 3). On sham stimulation, an eight-word false stimulation coil that can simulate sound and touch, such as Air film, which does not induce any significant physiological transcranial effect on the brain, will be used. The sham parameters will be set to 80% RMT, 50 Hz, 3 intra pulses, 5 Hz and 200 stimulus clusters [49]_._ Treatment will be twice daily. The PT training method and duration are as for the study group.

**Fig. 3 Fig3:**
[figure not shown]
The sham-iTBS + PT group

If the patient suffers an unbearable headache, we will reduce the intensity of the intervention to 40 Hz or below; if more serious side effects occur, we will choose the parameters suitable for the patient’s tolerance or stop the treatment altogether. Doctors and therapists will report adverse events during the intervention in writing to the study group in the EDC system. Falls, injuries and harmful adverse events will also be reported due to the rules and regulations of Beijing Rehabilitation Hospital, Capital Medical University.

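### The headache rule lowers intensity to a value in Hz, but the protocol sets intensity in % RMT and uses Hz only for frequency

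*Protocol article*

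**What the plan says.** Three places in the Methods of the protocol article bear on this.

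- **Active arm** (iTBS + PT group, parameters following Fig. 2). Intensity is "80% resting movement threshold (RMT) stimulation intensity". The pulse pattern is "triplet 50 Hz bursts, repeated at 5 Hz for 2 s on and 8 s off, 10 times". In the threshold measurement that follows, intensity again means the stimulator setting: "the transcranial magnetic stimulation output intensity is gradually adjusted".
- **Sham arm** (Sham-iTBS + PT group). The same quantities are listed separately: "The sham parameters will be set to 80% RMT, 50 Hz, 3 intra pulses, 5 Hz and 200 stimulus clusters".
- **Tolerability** (text following Fig. 3, at the end of the sham-arm section). If the patient has an unbearable headache, "we will reduce the intensity of the intervention to 40 Hz or below". A second step follows: "if more serious side effects occur, we will choose the parameters suitable for the patient’s tolerance or stop the treatment altogether".

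**The concern.** The headache step tells the operator to lower one quantity and gives the target in the unit of another. Intensity and pulse frequency are separate settings in this protocol, each with its own value. An operator who follows the number and one who follows the word would change different settings.

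Two things are at stake. The first is tolerability: a patient who reports an unbearable headache may get a change that leaves the named parameter where it was. The second is consistency of treatment: the modification could depend on how each operator reads the sentence. This is an instruction for use during sessions, and the Trial status section says that recruitment is ongoing.

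**Working it through.** This is a check of units and definitions. The plan states no figure that needs to be reproduced.

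**Inputs, all from the Methods of the protocol article**

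| Quantity | Active arm | Sham arm | Headache rule |
|---|---|---|---|
| Intensity | 80% RMT | 80% RMT | word used, no % RMT value |
| Pulse frequency within the triplet | 50 Hz | 50 Hz | not named |
| Repetition rate of triplets | 5 Hz | 5 Hz | not named |
| Stated target | – | – | 40 Hz or less |

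**Step 1. Does any section define an intensity in Hz?** No. In the two stimulation paragraphs, Hz denotes frequency only. The same holds in the Background (high- and low-frequency rTMS) and in the EEG section (filter band and sampling rate). The 40 Hz figure appears only in the headache rule and is not explained.

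**Step 2. Try each quantity that the rule could mean.**

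(a) *Intensity.* The starting value is 80% RMT. A value in Hz has no place on a % RMT scale and the article gives no conversion, so the operator has no target.

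(b) *Pulse frequency within the triplet.* The starting value is 50 Hz. Pulse spacing is 1000 / frequency in ms:
- at 50 Hz, 1000 / 50 = 20 ms;
- at 40 Hz, 1000 / 40 = 25 ms.

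A triplet has two gaps, so its span goes from 2 × 20 = 40 ms to 2 × 25 = 50 ms, or longer at frequencies below 40 Hz. This can be carried out, but it changes the pulse pattern and leaves intensity at 80% RMT, which contradicts the rule's own word.

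(c) *Repetition rate of triplets.* The starting value is 5 Hz. Since 5 ≤ 40, the condition is already met before any change, and the rule would do nothing.

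**Step 3. Compare.** No reading satisfies both the word and the unit. Reading (a) keeps the word and loses the target. Reading (b) keeps the number and loses the word. Reading (c) has no effect. The error could be a wrong unit attached to intensity or a wrong noun attached to frequency, and the article does not say which.

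**The case against.** The strongest reply is that the rule can be followed by its number. It speaks of the intensity of the intervention, a looser phrase than stimulation intensity, which might mean the strength of treatment as a whole. Only one frequency setting lies above 40 Hz, the 50 Hz within the triplet, so an operator could take that as the setting to lower. This stands in part: reading (b) is executable, and it is too strong to say that the sentence cannot be applied at all. But it depends on setting aside the meaning that the article itself gives to intensity, and a second operator could as reasonably lower the output instead.

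Several wider conclusions may tempt a reader. The document does not support them.

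- *The whole safety provision fails.* It does not. The step for more serious effects, "we will choose the parameters suitable for the patient’s tolerance or stop the treatment altogether", has no unit conflict and remains usable.
- *Unblinded operators choose parameters freely, so the comparison is biased.* The free choice belongs to the step for more serious effects, not to the headache step. The Blinding section discloses that the doctors giving iTBS know the allocation, and Data collection says that raters are blinded. Neither contradicts the headache rule.
- *Modified patients have no defined place in the analysis.* Statistical analysis already makes intention-to-treat primary. Detailed per-protocol rules and data-capture fields are commonly left to documents not shown here.
- *The rule differs by arm.* It stands at the end of the sham-arm section but refers to the patient without naming an arm, and no section gives different rules.

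**Conclusion.** The point holds as an internal contradiction confined to the headache step. The word and the unit conflict with the stimulation settings of both arms, and nothing else in the article resolves it. The conclusion rests on the printed wording alone and needs no assumption about rates or effects.

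Its size is qualitative. It touches any patient who triggers the step. A reader might want a count, but the article gives no frequency of unbearable headache, so any number would be a guess. Sample size, power and the primary analysis are not affected, and no effect on the primary estimate is shown. It should still be corrected, because the sentence governs what is done for a patient in discomfort while the trial is running.

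**What to change.** The sponsor's clinical team should reconcile the headache sentence with the stimulation parameters of the two arms: state which parameter is changed, and express the change in the unit in which the protocol defines that parameter. Which parameter and what value are clinical decisions for the sponsor, and none is proposed here.

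The cost is one corrected sentence. Under the Data monitoring section, a protocol amendment needs ethics committee approval before it is implemented. No change to the sample size or the analysis follows.

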### Primary outcome measures

The primary outcome will be the change in the third part of Movement Disorders–Unified Parkinson’s Disease Rating Scale (MDS-UPDRS III) from the baseline to the first 2 days following completion hospitalised intervention. MDS-UPDRS III [50] contains 18 items and each item was rated 0 to 4 points. The higher the scores, the poorer the motor symptoms (MS).

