### Data collection

At baseline, the following data will be collected: gender, age, occupation, education level, current medication status, detailed physical and neurological examinations. Inclusion and exclusion criteria will be evaluated. MDS-UPDRS III will be evaluated at T0 and T1. The PDQ-39 will be evaluated at 4 weeks, 12 weeks and 24 weeks after intervention. NMSS will be assessed at T0, T1, T2, T3 and T4. The 6MWD, 10MT, TUG, BBS, MRI and EEG will be scanned at T0 and T1. All the above assessments are evaluated blindly by the raters, who are unaware of the treatment methods used by the patients (Figs. 2 and 4).

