### Statistical analysis

SPSS v22.0 software (SPSS Inc., Chicago, IL, USA) will be used for data processing and analysis. Measurement data are expressed as mean ± standard deviation. The intention-to-treat (ITT) analysis will be the primary analysis of this study, and per-protocol(PP) analysis will be a secondary analysis if there are patients that did not receive the intervention because of problems of the intervention itself: adverse effects, difficult administration or adherence, etc. The missing data will be processed using the last observation carried forward (LOCF).The sensitivity analyses will be used if there are unbalanced losses to follow up or if too many losses, etc. The significance level for each test will be set at *P* < 0.05.

MRI pre-processing will be carried out using the data processing assistant for Rs-fMRI, which runs with the statistical parametric mapping software (SPM82) [64]. After the EEG data is recorded, it is processed offline through MATLAB software scripts and the EEGLAB toolbox [64].

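### The dropping criterion and a T1 visit timed from completion leave non-finishers with no defined primary outcome rating, although ITT is the primary analysis

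*Protocol article*

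**What the plan says.** All references are to the Methods of the protocol article.

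- **Primary outcome measures:** change in MDS-UPDRS III "from the baseline to the first 2 days following completion hospitalised intervention".
- **Data collection:** "MDS-UPDRS III will be evaluated at T0 and T1". T1 is therefore the only post-baseline value of the primary measure.
- **Study design and Follow-up:** T1 is placed 2 days after the intervention. No separate date is given for a patient who stops early.
- **Intervention:** baseline is days 1-2 and treatment is days 3-12.
- **Dropping criteria:** two are listed. One is not completing the training, in either group; the other is worsening that calls for a change of drugs.
- **Sham-iTBS + PT group, text after Fig. 3:** for more serious side effects, "we will choose the parameters suitable for the patient’s tolerance or stop the treatment altogether".
- **Statistical analysis:** "The intention-to-treat (ITT) analysis will be the primary analysis of this study". The per-protocol "analysis will be a secondary analysis if there are patients that did not receive the intervention because of problems of the intervention itself". Missing data are handled by LOCF.
- **Sample size:** 21 per group, raised to 50 in total for 12% dropout.

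**The concern.** Two rules select patients who complete the course: the dropping criterion, and a primary endpoint visit counted from completion. The analysis section promises a comparison of everyone randomised. A site applying the first two literally to a patient who stops on day 5 is told to drop that patient and has no T1 date to work to. Yet the patient was admitted for a 10-day course and could have been rated.

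The result would be a missing primary outcome in some of the patients whom ITT is meant to keep. No imputation method recovers a rating that was never taken. LOCF in particular has nothing to carry forward but the baseline. Both arms receive physiotherapy, so a change of exactly zero is not a neutral value.

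**Working it through.** **1. The plan's own figure.** Inputs from Sample size: difference 4.89, SD 4.88, power 90%, alpha 0.05 (taken as two-sided, which reproduces the stated figure).

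n per group = 2 × [4.88 × (1.960 + 1.282) / 4.89]² = 20.93, rounded up to 21. Then 21 / 0.88 = 23.9, so 24 per group or 48 in total; the stated 50 is within 2 patients. The sample size is not in question. The 12% is an overall allowance: 0.12 × 50 = 6 patients. It is not tied to the T1 visit.

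**2. What LOCF does here.** With ratings only at T0 and T1, a patient without T1 has the T0 score carried forward, so the change is T0 - T0 = 0.

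**3. Expected difference under LOCF.** Let c be the mean change in sham finishers, c - 4.89 the mean change in active finishers, and p1 and p0 the proportions of non-finishers in the active and sham arms. Then:

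LOCF difference = (1 - p1)(c - 4.89) - (1 - p0)c = -4.89(1 - p1) + (p0 - p1)c

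The article does not give c. I assume a range of 0 to -4 points. As a reference, suppose that non-finishers in either arm, had they been rated, would have changed as sham finishers did. The true difference is then -4.89(1 - p1), and the error from LOCF is (p0 - p1)c.

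**4. Results.** There are 25 per arm and finishers' SD is 4.88. Each row has 6 non-finishers in total. Power is Φ(|difference|/SE - 1.96), with SE² = (v1 + v0)/25. Each arm's variance is v = (1 - p)(4.88² + m²) - [(1 - p)m]², where m is that arm's finisher mean.

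| Non-finishers, active / sham | Reference | LOCF, c = 0 | LOCF, c = -4 | Power, c = 0 to c = -4 |
|---|---|---|---|---|
| 12% / 12% (3 / 3) | -4.30 | -4.30 | -4.30 | 90% to 85% |
| 20% / 4% (5 / 1) | -3.91 | -3.91 | -3.27 | 82% to 60% |
| 4% / 20% (1 / 5) | -4.69 | -4.69 | -5.33 | 95% to 97% |

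At c = -4 the error is (0.04 - 0.20) × (-4) = +0.64 in the second row, against iTBS. In the third row it is (0.20 - 0.04) × (-4) = -0.64, in favour of iTBS. With equal proportions it is zero.

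**The case against.** **Silence is not a rule.** A reader might infer that no T1 score is taken in non-finishers. The article does not say so. It does not state whether dropping ends treatment, assessment or inclusion in the analysis, and it lists T1 as a general visit. A per-protocol analysis for patients who did not receive the intervention implies that such patients stay in the ITT set. This objection stands: missing T1 ratings are the plain reading, not a stated fact.

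**Training may mean physiotherapy only.** The article describes the physiotherapy as training, whereas the instruction to "stop the treatment altogether" follows a sentence on stimulation intensity. A patient who stops iTBS might still finish physiotherapy and reach T1. This also stands. Loss of outcomes because active stimulation is not tolerated is possible but not established.

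**Inflation of the effect does not follow.** A reader might infer that dropping intolerant active patients must overstate the benefit. That holds for a finishers-only comparison, which the article does not name as primary. Suppose 3 of 25 active patients stop, none stops in sham, and stoppers do as sham does. The true difference is 4.89 × 22/25 = 4.30. LOCF gives 4.30 at c = 0, and 22/25 × 8.89 - 4 = 3.82 at c = -4: no bias, or bias against iTBS.

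**Expected missing T1 ratings are not given.** The 12% allowance is not linked to T1, and participation lasts 26 weeks. It should not be read as 6 patients expected to lack a primary outcome.

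**The full protocol may hold visit rules for early stoppers.** It may, and their absence from an article alone would be no finding. The dropping criterion, however, is a stated rule. As worded, it works against the stated primary analysis.

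**Conclusion.** The concern holds as an unresolved conflict between the Dropping criteria, the timing of the primary outcome and the primary ITT analysis. On a plain reading, non-finishers have no observed primary outcome. They would be counted as zero change through LOCF, or excluded if dropping means removal from the analysis.

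Neither the direction nor the size of bias can be fixed from the documents. In the splits examined, LOCF misses the reference by up to 0.64 points either way. This rests on an assumed sham change of 0 to -4, on non-finishers changing as sham finishers do, and on splits of 6 non-finishers chosen for illustration. The documents do not support a claim that the effect will be overstated. The planned sample size is unaffected.

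**What to change.** Reconcile Dropping criteria, Primary outcome measures and Statistical analysis:

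1. State that meeting a dropping criterion does not end outcome assessment.
2. Date T1 by the planned end of the course for every randomised patient who still consents, whether or not the course was finished. With treatment on days 3-12, this is days 13-14.
3. Use non-completion only to define the per-protocol set.

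The rules for stopping treatment or changing drugs stay as they are, and N does not change.

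The cost is amendment wording, ethics committee approval and one motor rating that is already scheduled. At the planning inputs, normal-approximation power is 91.4% with 22 measured per arm and 94.3% with all 25, so full measurement may recover some information; that figure assumes the planned effect applies to everyone measured. Some early stoppers may decline the rating. Enrolment began in April 2022, so T1 scores of non-finishers already dropped may not be recoverable. Any such patients should be counted and reported by arm.
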